## Methods and analysis

### Design

PAX-D is a multisite, double-blind, placebo-controlled, randomised trial evaluating the effects of the addition of pramipexole to antidepressant treatment in patients with TRD. Participant involvement in the trial will have two phases, a pre-treatment, pre-randomisation, run-in phase and a postrandomisation 48-week treatment phase (see figure 1). The run-in phase will assess potential participants’ ability to complete study activities and to mitigate baseline inflation effects on outcome measures. Since there is no widely accepted, first-line treatment for TRD, the comparator in the current trial will be addition of placebo. Participants will be randomised to receive either pramipexole or placebo at the randomisation visit. Participants, investigators and the trial team will remain blind to allocation. Pharmacy staff will be unblinded for dispensing purpose.

**Figure 1 F1:**
[figure not shown]
Participant timeline. GAD-7, General Anxiety Disorder Scale 7; RA, research assistant; SHAPS, Snaith-Hamilton Pleasure Scale; QIDS, quick inventory of depressive symptomatology; QUIP-RS, Questionnaire for Impulsive-Compulsive Disorders in Parkinson’s Disease-Rating Scale.

### Recruitment

Participants will be recruited from primary and secondary care services associated with the trial sites or by self-referral. The study will be advertised to local clinicians and in local and online media. Following a single-site internal pilot at the Oxford Health National Health Service (NHS) Foundation Trust, recruitment will continue in four additional sites across the UK (Newcastle, Bristol, Kings College London and University College London), and then extended to other NHS mental health trusts in regions around these sites as needed.

### Eligibility

The eligibility criteria are summarised in figure 2. During the study visits, participants will be assessed by a research assistant (RAs) and a psychiatrist.

**Figure 2 F2:**
[figure not shown]
Eligibility criteria. RA, research assistant; QIDS-SR16, quick inventory of depressive symptomatology self-report.

### Interventions

In the Pramipexole for depression (PAX-D) trial, pramipexole will be added to an antidepressant that the participant is prescribed outside of the trial. The psychiatrist will be responsible for trial medication prescription. Pramipexole tablets will be taken orally. All dosages are reported as pramipexole salt (NB 1 mg of pramipexole salt is equivalent to 0.7 mg of pramipexole base). Pramipexole dihydrochloride monohydrate will be initiated at 0.25 mg/day and, in the absence of concerns about tolerability, the dose will be increased by 0.25 mg/day every 3 days towards a target dose of 2.5 mg/day (see online supplemental material for titration schedule). The target dose was selected to be at the upper end of those used in previous trials^6–10^ as the case series of TRD patients reported by Fawcett *et al*
10 indicated that a number of patients responded to higher doses. The titration schedule was also based on the Fawcett case series.^10^ The titration schedule may be amended at the discretion of the treating psychiatrist. Specifically, participants who are unable to tolerate an increased dose of pramipexole, for example, due to adverse effects, will be advised to reduce the dose to the highest tolerated. Participants will remain on this highest tolerated dose throughout the remainder of the trial. No re-titration will be attempted. Any dose reductions will be tapered every 3 days. This will reduce the risk of developing dopamine agonist withdrawal syndrome. For more information on managing adherence, discontinuing, modifying allocated interventions and concomitant treatments (see online supplemental material).

10.1136/ebmental-2021-300282.supp1Supplementary data

#### Assignment of intervention

Each participant will be randomised at a ratio of 1:1 to either pramipexole or a matched placebo. A non-deterministic algorithm will be used to produce treatment groups balanced for important prognostic factors by minimising separately on four variables including (1) trial site, (2) age (18–50, vs >50), (3) gender (M/F) and (4) baseline quick inventory of depressive symptomatology self-report 16 (QIDS-SR16) severity (11–15 vs 16–20 vs >20).

### Outcomes

Questionnaires will be administered through a combination of participant self-reports, semi-structured interviews and completion by a psychiatrist during a clinic visit. Participants will complete questionnaires electronically using True Colours, an online platform accessed using electronic devices.^17^ Participants will be telephone contacted by an RA at screening, weekly from week 0 to 12, then 4-weekly up to week 48 to complete semi-structured interviews asking about adverse effects including any increase in impulsive behaviour or suicidality, any changes in medication and any problems with adherence.

#### Decision-making task

The task^16^ consists of 3 runs of 60 trials each (180 trials in total). On each trial, participants are presented with two abstract shapes (letters selected from the Agathodaimon font) and choose the shape which they believe will result in the best outcome. Two shapes are presented during ‘win trials’ and may result in winning either 20 or 0 points (with one shape leading to a win of 20 points on 70% of trials and the other shape on 30% of trials). A separate pair of shapes are associated with ‘loss trials’ and may result in losing 20 or 0 points (with one shape leading to a loss of 20 points on 70% of trials and the other shape leading to a loss on 30% of trials). The shapes used change in each run of the task. Participants must learn from the outcome of previous trials what they think the best shape to choose is. An increased reward sensitivity may cause participants to more consistently select the high probability rewarding outcome in the last half of each block, and is estimated by fitting a standard reinforcement learning model with free parameters for learning rates and outcome sensitivity to participant choices during the win trials. Participants will complete the task via True Colours on a computer during study visits at screening (practice), week 0 (Randomisation), week 2 and 12.

#### QIDS-SR16 and clinician-rated (QIDS-C)

This is a 16-item questionnaire that covers 9 symptoms of depression.^18^ The scale assesses severity of depression and change in depressive symptoms over time. Participants are instructed to score each item according to the description that best describes their experience over the past 7 days. Each of the symptoms is scored on a 4-point scale (0–3) giving a maximum possible score of 27 (not all items contribute to the total). The total score will detect change in depression symptom-severity, while item 12 will additionally act to detect suicidal thoughts. Clinicians will complete QIDS-C during all study visits. Meanwhile, participants will complete QIDS-SR16 on True Colours once per week from screening to Week 12, and then once every 4 weeks up to week 48.

#### Altman Self-Rating Mania Scale (ALTMAN)

This is a 5-item self-report questionnaire that assesses any change in the severity of symptoms of mania.^19^ Participants are instructed to score each item according to the description that best describes how they have been over the past 7 days. Each of the symptoms is scored on a 5-point scale (0–4) giving a maximum score of 20. Participant will complete ALTMAN on True Colours at screening, weekly from randomisation to week 12, and then 4-weekly up to week 48.

#### General Anxiety Disorder Scale-7

This seven-item self-report questionnaire screens for symptoms of anxiety and measures severity.^20^ Assessment is derived from the total score across all seven items. Participant will complete this on True Colours at screening, weekly from randomisation to week 12, and then 4 weekly up to week 48.

#### Snaith-Hamilton Pleasure Scale

This is a 14-item scale that measures anhedonia, the inability to experience pleasure.^21^ The items cover the domains of: social interaction, food and drink, sensory experience and interest/pastimes. Each item has four possible responses: strongly disagree, disagree, agree or strongly agree. Either of the ‘disagree’ responses score 1 point, and either of the ‘agree’ responses score 0 points. The final score ranges from 0 to 14, with higher scores indicating higher levels of anhedonia. Participant will complete this on True Colours at screening, 2-weekly from randomisation to week 12, and then 4-weekly up to week 48.

#### UCLA Loneliness Scale

This questionnaire comprises three questions that measure three dimensions of loneliness: relational connectedness, social connectedness and self-perceived isolation.^22^ The scale uses three response categories: ‘Hardly ever’ (scoring 3)/‘some of the time’ (scoring 2) /‘often’ (scoring 1). The scores are added together to give a total score (3 to 9). Participants will complete this scale on True Colours at week 0, 6, 12 and 48.

#### English Longitudinal Study of Ageing social isolation measure

This measure is derived from the English Longitudinal Study of Ageing, a nationally representative panel study of people aged 50 years or older living in England.^23^ It is a widely used measure of social isolation, often employed with some modifications. In PAX-D, the whole scale will be collected for the baseline measure, then for weeks 6, 12 and 48 the first three response options will be collected (3+times per week, 1–2 per week, 1–2 per month) with a change of the fourth response to ‘not in the past month’. Participants will complete this measure on True Colours at week 0, 6, 12, 48.

#### Treatment Satisfaction Questionnaire for Medication Version 9

The 9-item Treatment Satisfaction Questionnaire for Medication (TSQM)^24^ assesses patient-reported satisfaction of their medication. The domains covered are convenience, effectiveness and global satisfaction. Each item is rated on a seven or five-point scale. TSQM-9 will be completed during RA telephone contact at week 0, 6, 12, 24 and 48.

#### Questionnaire for Impulsive–Compulsive Disorders in Parkinson’s Disease-Rating Scale

The Questionnaire for Impulsive-Compulsive Disorders in Parkinson’s Disease–Rating Scale (QUIP-RS)^25^ has four primary questions (pertaining to commonly reported thoughts, urges/desires, and behaviours associated with impulse control disorders), each applied to the four impulse control disorders (compulsive gambling, buying, eating, and sexual behaviour) and three related disorders (medication use, spending and hobbyism). It uses a 5-point Likert scale (score 0–4 for each question) to gauge the frequency of behaviours. QUIP-RS will be completed at screening and then during RA contact weekly from week 0 to 12, then 4-weekly up to week 48.

#### Work and Social Adjustment Scale

This measures the impact of a respondent’s mental health difficulties on their ability to function in terms of five dimensions (work, home management, social leisure, private leisure and personal or family relationships).^26^ Severity is measured on an eight-point Likert scale (ranging from ‘not at all’ to ‘very severely’. The total Work and Social Adjustment Scale (WSAS) score is derived by adding the scores across all the items. Participants will complete WSAS on True Colours 4-weekly from week 0 to week 12, then at week 24, 36, and 48.

#### EQ-5D-5L

This is a standardised measure of health status and provides a generic measure of health-related quality of life for clinical and economic appraisal (https://euroqol.org/eq-5d-instruments/eq-5d-5l-about/). The scale has five dimensions (mobility, self-care, usual activities, pain/discomfort and anxiety/depression) and five levels for each dimension (no problems, slight problems, moderate problems, severe problems, extreme problems. A visual scale records the respondent’s self-rated health with endpoints labelled ‘the best health you can imagine’ and ‘the worst health you can imagine’. Participants will complete EQ-5D-5L on True Colours at week 0, 12, 24, 36 and 48.

#### ICEpop CAPability measure for Adults

This is a measure of capability for the adult (18+) population for use in economic evaluation.^27^ The measure covers attributes of well-being that were found to be important to adults in the UK. It has five dimensions (attachment, stability, achievement, enjoyment and autonomy) and assesses broader well-being. Participants will complete ICEpop capability measure for adults (ICECAP-A) on True Colours at week 0, 12, 24, 36 and 48.

#### Oxford CAPabilities questionnaire-Mental Health

This is a validated mental health specific capability well-being scale with 16 items.^28^ The items cover different domains of well-being (overall health, social and recreational activities, loss of sleep due to worry, friendship and support, having suitable accommodation, feeling safe, likelihood of discrimination and assault, freedom of personal and artistic expression, appreciation of nature, self-determination, and access to activities or employment), each scored on a 5-point Likert scale. Participants will complete Oxford CAPabilities questionnaire-Mental Health (OxCAP-MH) on True Colours at week 0, 12, 24, 36 and 48.

Health Economics Questionnaire (HEQ). The HEQ has specifically been developed for mental health economic evaluations and is now also complemented with a COVID-19-related module (https://zenodo.org/record/4559752). It measures health and social care resource use, medication, absenteeism from work and presenteeism as well as sociodemographic background information. Participants will complete this on True Colours at week 0, 12, 24, 36 and 48.

### Sample size

At week 12, PAX-D considers a three-point difference on QIDS-SR_16_ scores between pramipexole and placebo to be clinically important (with SD of the scores of 5.4 based on those observed in the CEQUEL trial^29^ and produces a standardised effect size of 0.56). The sample size to test differences between groups at 90% power and at a type one error rate of 5% would be 68 per group (136 total), increasing with 20% drop-out to 170 total. To test a similar sized difference in reward sensitivity and to ensure that type one error for both the depression score and the reward sensitivity tests is 0.05 or below, the sample size calculation can be determined using an alpha of 0.025. At an alpha of 0.025 and power of 90%, the required sample size would be 81 per group. Allowing for an estimated 20% lost to follow-up would then increase the sample size to 102 per group (204 total).

### Statistical methods

The primary outcome (change in QIDS-SR16 between baseline and week 12) will be analysed using a generalised linear mixed model utilising data collected at each weekly time point from randomisation and including the baseline outcome and minimisation factors as fixed effects. The model will include a random intercept for each participant to account for the repeated measures on the same participant and an interaction term for the treatment by time interaction to allow the treatment effect to differ at each time point.

Continuous secondary outcomes will be analysed using generalised linear models. The dichotomous secondary outcomes will be analysed using a logistic mixed effects regression model. These analyses will include a fixed effects randomised group and baseline level of the QIDS-SR_16_, with participants and trial site accounted for as random effects. Minimisation variables will be included as explanatory factors in the models. Mediational analysis will test whether changes in reward sensitivity mediate the effect of pramipexole on depressive symptoms. Health economic data analysis will assess group differences in quality of life, well-being, and work performance using a cost-utility analysis.

The primary and efficacy-based secondary analyses will be performed using an intention-to-treat approach for all randomised participants. Analyses of the mechanistic secondary outcomes and health economic outcomes will be performed in the set of participants who have the data required for the specific analyses (ie, no imputation will be performed for these analyses). Acceptability analyses will be performed on a subgroup of participants and trial clinicians who provide separate consent for aspect of the trial.

The main health economic analysis will include: (1) a detailed patient-level cost analysis of health, social care and other broader societal costs for both the pramipexole and placebo arms of the trial and (2) an incremental within-trial economic evaluation comparing the pramipexole and placebo arms of the trial in terms of their costs and outcomes over the 48-week trial follow-up period.

The primary health economic analysis will be a cost-utility analysis from a health and social care perspective where quality-adjusted life-years will be calculated using utility values from the EQ- 5D-5L. Secondary economic analyses using the ICECAP-A and the OxCAP-MH capability indices as outcome measures will be also carried out. Further analyses will estimate cost-effectiveness from a societal perspective. All economic analyses will be on an intention-to-treat basis.

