### Objectives

The primary objective of PAX-D is to assess the efficacy of adding pramipexole to conventional antidepressant medication for treating symptoms of depression. Pramipexole will be administered under double-blind, placebo- controlled conditions in patients with TRD. Second, PAX-D will examine the effect of pramipexole on reward sensitivity and whether this may predict treatment outcome. A decision-making task^16^ will be used in the current trial to measure the impact of pramipexole on reward sensitivity. The relationship between pramipexole treatment, change in reward sensitivity and symptomatic response will be formally assessed using a mediation analysis. Further, the trial will estimate the degree to which baseline and initial changes in reward sensitivity are able to predict response to pramipexole, providing a first test of the potential for these measures to be deployed in the selection of treatments for TRD patients. Finally, PAX-D will conduct an economic analysis of pramipexole and its longer-term effect on quality of life, capability, well-being, functioning and costs. Finally, the acceptability and tolerability of pramipexole will be assessed across the course of treatment. All objectives are summarised in table 1.

**Table 1 T1:** Study objectives (from https://www.isrctn.com/ISRCTN84666271)

Objectives	Outcome measures	Time points
Primary objective	Primary outcome	
To compare the efficacy of pramipexole and placebo at 12 weeks postrandomisation	Improvement (change from baseline) of depressive symptoms measured on the QIDS-SR_16_	Week 1–12
Secondary objectives	Secondary outcomes	
To compare the tolerability and safety of pramipexole and placebo during the 48-week treatment phase	Tolerability assessed by: Termination of trial treatment due to intolerance Adverse reactions TSQM-9 Safety–emergence of new symptoms: ALTMAN (manic symptoms) QUIP-RS (impulse control) Suicidal ideation (QIDS-SR_16_)	Weeks 1–48
To compare the effect of pramipexole and placebo on reward sensitivity	Change in reward sensitivity parameter from model fitted to learning/decision making task between baseline, week 2 and week 12	Baseline, week 2, week 12

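### The primary model handles the weekly QIDS-SR16 scores with a participant random intercept and names no other covariance term; with default residuals, the week-12 standard error is too small if spread grows over the weeks

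*Protocol article*

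**What the plan says.** The primary objective (Table 1) is "To compare the efficacy of pramipexole and placebo at 12 weeks postrandomisation". The questionnaire is frequent: "participants will complete QIDS-SR16 on True Colours once per week from screening to Week 12".

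Statistical methods fits one mixed model to the change in QIDS-SR16, "utilising data collected at each weekly time point from randomisation and including the baseline outcome and minimisation factors as fixed effects". The within-participant structure is stated: "The model will include a random intercept for each participant to account for the repeated measures on the same participant". The model also has "an interaction term for the treatment by time interaction to allow the treatment effect to differ at each time point", so the week-12 effect is one contrast among twelve post-baseline weeks.

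The section does not mention a random slope, week-specific variances, another residual structure or robust standard errors. The only information on spread is in Sample size: "with SD of the scores of 5.4 based on those observed in the CEQUEL trial".

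**The concern.** A random intercept with independent, constant-variance residuals gives every week the same variance and every pair of weeks the same correlation, so weeks 1 and 12 are as alike as weeks 11 and 12. With a free treatment effect at each week and complete data, the week-12 estimate is essentially the adjusted mean difference at week 12. Its standard error, however, is built from the variance averaged over all twelve weeks. If participants are close together early, once baseline is taken into account, and further apart by week 12, the average is smaller than the week-12 variance.

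At stake is the primary test: the p-value would be too small and the interval too narrow. Sample size deliberately tightens alpha to 0.025, raising the total from 170 to 204, to protect the type I error. An understated standard error could use up some of that protection.

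**Working it through.** **The plan's own figures.** Inputs from Sample size: difference 3, SD 5.4, power 90%. Formula: n per group = 2 × (5.4/3)² × (z₁₋α/₂ + z₀.₉₀)².

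- α = 0.05: 6.48 × (1.960 + 1.282)² = 68.1 (stated 68; strict rounding up gives 69). 136/0.8 = 170 total.
- α = 0.025: 6.48 × (2.241 + 1.282)² = 80.4, so 81. 81/0.8 = 101.25, so 102 per group and 204 total.

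These reproduce. They rest on the week-12 SD alone, with standard error 5.4 × √(2/81) = 0.849, so the covariance question does not touch them.

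**Model against true standard error.** Complete data, n per group, T = 12 weeks, baseline-adjusted SD σ_t at week t:

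- model SE = √(2 × mean of σ_t² / n)
- true SE = √(2 × σ₁₂² / n)
- ratio R = √(mean of σ_t² / σ₁₂²)
- true type I error = 2 × (1 − Φ(z × R))

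**Worked case (assumed SDs).** SD rises linearly from 4.0 to 5.0. Mean variance = 4.5² + 1² × 13/132 = 20.35. R = √(20.35/25) = 0.902. At nominal 5%, 1.960 × 0.902 = 1.768, giving a true level of 7.7%.

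**Range, SD 5.0 at week 12, nominal 5%.** The path of the rise is also an assumption.

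| Week-1 SD | R, linear to week 12 | True level, linear to week 12 | Rise complete by week 6 | Rise complete by week 4 |
|---|---|---|---|---|
| 4.5 | 0.95 | 6.2% | 5.6% | 5.4% |
| 4.0 | 0.90 | 7.7% | 6.2% | 5.8% |
| 3.5 | 0.86 | 9.4% | 6.8% | 6.1% |
| 3.0 | 0.81 | 11.2% | 7.4% | 6.5% |

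At nominal 2.5%, the last row with a linear rise gives 7.0%.

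**Other directions, SD 5.4 at week 12.** Constant SD: R = 1.00, level 5.0%. SD falling linearly from 6.0: R = 1.06, level 3.9%, which is conservative.

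**Why growth is plausible.** The raw SD need not grow. If r_t is the correlation of week t with baseline, the variance left after adjustment is about SD² × (1 − r_t²), which rises as r_t falls. With constant raw SD and r falling linearly over weeks 1 to 12 (assumed values):

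- 0.8 to 0.5: R = 0.87, level 8.8%
- 0.7 to 0.4: R = 0.91, level 7.6%
- 0.6 to 0.4: R = 0.94, level 6.5%
- 0.5 to 0.3: R = 0.96, level 6.0%

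The minimisation strata also begin at a score of 11, so baseline is restricted from below and later scores are not.

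**Simulation check.** The random-intercept model was fitted by REML to 1000 null trials per setting, so the Monte Carlo error near 5% is √(0.05 × 0.95/1000) = 0.7 points.

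- SD 3.5 rising to 5.4, complete data, 81 per group: mean model SE 0.70 to 0.71 against an empirical 0.84 to 0.85; rejection 10.6% to 12.0% (closed form 10.3%).
- Constant SD and exchangeable correlation, with or without 20% dropout: rejection 4.9% to 5.4%.
- Constant SD, AR correlation 0.9, 20% dropout, 102 per group: rejection 7.7%. Other constant-SD runs went as low as 4.5%, so the added effect of dropout is not settled.

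**The case against.** The strongest reply is that the article says the model will include a random intercept, not that it has nothing else. Heterogeneous or autocorrelated residuals, or robust standard errors, can sit beside a random intercept, and such detail commonly belongs in the analysis plan, which is not shown. This stands in part. That the intercept is the sole term is an inference, and a later plan may already have dealt with it. But the article is not silent: it gives the random intercept as the means of handling repeated measures, and a plan that follows it literally inherits the problem.

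Second, growth in spread is not documented. There is one SD and no weekly SDs or correlations, and the size of the error depends on the assumed path. This stands fully, and it is why the result is a range that includes zero error and a conservative test.

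Third, the practical reach is limited. With complete data the week-12 estimate does not move. Under simulated dropout its bias was 0 to 0.2 points, against the article's target: "At week 12, PAX-D considers a three-point difference on QIDS-SR_16_ scores between pramipexole and placebo to be clinically important". This also stands; the issue is the standard error.

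A reader might infer that the planned alpha is not delivered, or that the trial is under-sized. The documents support neither. The first holds only if spread grows and default residuals are used; the second is ruled out because the sample size does not depend on the covariance model.

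**Conclusion.** The concern holds conditionally. As worded, and with default residuals, the primary model gives the week-12 contrast a standard error pooled over weeks 1 to 12. If baseline-adjusted SD rises to 5.0 from between 4.5 and 3.0, the true level at nominal 5% is about 5.5% to 11%: the upper end needs a steep rise that continues to week 12, the lower end a small rise that is over early. If only the correlation with baseline decays, it is about 6.0% to 8.8%. The mechanism is certain under those residuals; the size is not, because every weekly SD and correlation used here is assumed. Severity: should-fix, with moderate confidence.

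**What to change.** State the within-participant covariance for the primary model. Either of these would do:

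- Use weeks 1 to 12 as the response vector, with week 0 as covariate only, and an unstructured covariance, REML and Kenward-Roger degrees of freedom. Name a fallback in advance if it does not converge: heterogeneous Toeplitz, then heterogeneous AR(1).
- Keep the random intercept and add week-specific residual variances, or use cluster-robust standard errors for the week-12 contrast.

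If the analysis plan already does one of these, bring the article's description and the plan into line.

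The cost is a sentence or two and a few lines of code; no extra participants are needed. An unstructured matrix for twelve weeks has 12 × 13/2 = 78 parameters, so the fallback may be used. The week-12 standard error may come out slightly larger.

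### The primary model as listed gives baseline QIDS-SR16 one slope for all weeks, so the week-12 contrast can be biased if that slope changes over time and baseline-related dropout differs by arm

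*Protocol article*

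**What the plan says.** Under Statistical methods, the protocol article describes the primary analysis as a mixed model "utilising data collected at each weekly time point from randomisation". The covariates of that model are given in the phrase "including the baseline outcome and minimisation factors as fixed effects". The article continues: "The model will include a random intercept for each participant to account for the repeated measures on the same participant". To this it adds "an interaction term for the treatment by time interaction to allow the treatment effect to differ at each time point". Treatment by time is the only interaction named.

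The minimisation factors (Assignment of intervention) include baseline QIDS-SR16 in three bands: 11–15, 16–20 and above 20. Baseline severity therefore enters twice, as a score and as a band. Neither is listed with a time interaction.

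Under Sample size, the target is set by "PAX-D considers a three-point difference on QIDS-SR_16_ scores between pramipexole and placebo to be clinically important". The variability is taken from an earlier trial: "SD of the scores of 5.4 based on those observed in the CEQUEL trial". The total of 204 is reached by "Allowing for an estimated 20% lost to follow-up". That loss is not split by arm or by severity.

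**The concern.** A baseline score usually predicts the score one week later better than the score twelve weeks later. If that is so here, a single slope fitted to all twelve weeks is an average that is too steep for week 12. While both arms keep the same baseline mix, the error cancels in the treatment contrast. It stops cancelling once patients of different baseline severity are lost from the two arms, because the week-12 means are then adjusted with the wrong slope.

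This would be an ordinary missing-at-random pattern driven by a covariate already in the model, which a likelihood-based analysis should handle. The fault lies in the mean model: using the true unstructured covariance instead of a random intercept left the bias nearly the same.

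Different dropout in the two arms is plausible. The Introduction reports heavy dropout at the highest dose of one earlier pramipexole trial, and a small combination group in which four patients completed. The Interventions section provides for dose reduction for intolerance. Patients could leave pramipexole mainly for side effects and placebo mainly for lack of benefit, and those reasons could relate differently to baseline severity. The documents do not say that they do.

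At stake is the primary estimate. Benefit would be understated if severe patients leave pramipexole and overstated if they leave placebo.

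**Working it through.** **1. The plan's own figures.** Difference 3, SD 5.4, so d = 3/5.4 = 0.556, stated as 0.56. For 90% power, two-sided, a t-test calculation at d = 0.56 gives 67.99 per group at alpha 0.05 (stated 68) and 80.4 at alpha 0.025 (stated 81). With 20% loss: 68/0.8 = 85 per group, 170 in total; 81/0.8 = 101.25, so 102 per group, 204 in total. The figures reproduce.

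**2. Model compared.** Outcome at weeks 1–12; fixed effects for week, treatment by week, baseline and severity band; random intercept per participant. It was fitted once with a single baseline slope and once with baseline by week. The band kept constant coefficients in both fits.

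**3. Assumptions, none from the documents.** Baseline mean 17, SD 3.5, truncated to 11–27; residual SD 4.5; true week-12 effect −3; 17–25% dropout per arm. The true baseline slope was constant at 0.6, or fell linearly from 0.9 to 0.5 or from 0.9 to 0.3. The log odds of weekly dropout changed by 0.7 per baseline SD (1.2 in the strong case). Each cell used three runs of 40,000 participants. Bias is the model estimate minus the full-data week-12 ANCOVA estimate; a positive value is towards no effect. Ranges cover constant and decaying residual correlation.

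| Dropout relation to baseline | Slope constant, single slope fitted | Slope 0.9 to 0.5, single slope fitted | Slope 0.9 to 0.3, single slope fitted |
|---|---|---|---|
| Same in both arms | 0.00 to 0.01 | −0.01 | −0.02 to 0.01 |
| Pramipexole only | 0.00 to 0.01 | 0.15 | 0.22 to 0.24 |
| Opposite in the two arms | −0.01 to 0.00 | 0.27 | 0.41 to 0.42 |
| Strongly opposite | 0.00 to 0.01 | 0.47 to 0.51 | 0.71 to 0.73 |

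With baseline by week added, the bias was within about 0.015 points in every cell. Reversing the dropout pattern reverses the sign.

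**4. At the trial's own size.** In 250–300 simulated trials of 204 participants per scenario, the slope fell from 0.85 to 0.45 or from 0.90 to 0.30 and 19–25% were lost. When severe patients tended to leave placebo (dropout hazard ratio per baseline SD 1.4–2.0 in placebo, 0.7–1.0 in pramipexole), the single-slope model gave −3.10 to −3.46, against −2.98 to −3.08 with baseline by week. The bias was 0.08 to 0.42 points. When severe patients left pramipexole (hazard ratio 1.7), the single-slope model gave −2.72 to −2.86. Further runs with about 21% loss gave errors of about 0.1 to 0.25 points.

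**5. What that means for the test.** The standard error implied by the sample size is 5.4 × √(2/81) = 0.85. A bias of 0.15 to 0.27 is 0.15/0.85 = 0.2 to 0.27/0.85 = 0.3 standard errors. Power at alpha 0.025 is Φ(effect/0.8485 − 2.241):
- effect 3: Φ(1.29) = 90%
- effect 2.85: Φ(1.12) = 87%
- effect 2.73: Φ(0.98) = 84%

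**6. Limit of the remedy.** Dropout was next made to depend on the last observed score, with residual correlation decaying at 0.9 per week. The random-intercept model still showed a bias of 0.07 to 0.16 points with baseline by week included. It did so even when the baseline slope was constant, so this part comes from the covariance and not from the baseline term.

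**The case against.** The strongest reply is that the article never says the baseline slope is held constant. It describes the model in two sentences and points to a fuller protocol (Data Availability), and the analysis plan is not shown. Whether each covariate interacts with week is often settled there. This stands in part: a reader might infer that the trial has ruled the term out, and the documents do not support that. They do, however, list the model's terms and single out treatment as the effect allowed to vary by time, so the specification on the page has one baseline slope.

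Second, a reader might infer that the week-12 contrast is biased whenever severity-related dropout differs by arm. That is not so. With a constant true slope the bias was nil under exactly that dropout pattern. No baseline–outcome slope or correlation is given for any week, so a falling slope is an expectation and not a documented fact.

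Third, a reader might take the 20% loss as something the plan says this model will handle. The Sample size section uses it only to inflate recruitment.

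Fourth, the size is modest in moderate scenarios, and the larger figures need strongly opposite dropout in the two arms. That also stands.

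**Conclusion.** The point holds in conditional form. As listed, the primary model frees the treatment effect by week but not the baseline effect. Bias in the week-12 contrast under missing at random then needs three things together: a baseline slope that changes over weeks 1–12, dropout related to baseline, and a relation that differs by arm. Under assumed moderate versions of these, with about 20% loss, the bias is roughly 0.1 to 0.4 points, or 0.1/3 = 3% to 0.4/3 = 13% of the target difference. Its direction cannot be known in advance. Without a changing slope, or with the same dropout relation in both arms, it is about zero.

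This is a weakness in the stated specification that is cheap to remove. It does not show that the trial's estimate will be biased, and the unseen analysis plan may already deal with it.

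**What to change.** In the primary model, add a baseline QIDS-SR16 by week interaction, with week categorical, alongside treatment by week, and fix this before unblinding. If the analysis plan already has the term, align the protocol text with it.

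The cost is 12 − 1 = 11 extra fixed-effect parameters, set against 204 × 12 = 2,448 possible weekly scores before loss. No extra data are needed. In the simulations at the trial's size, the term cost no precision when dropout was not arm-specific: the empirical SD of the estimate fell by up to 4%.

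The added term should not be presented as protection against all missing-at-random dropout. Where dropout follows post-baseline scores, the random-intercept-only covariance remains a separate limitation, and an unstructured covariance would be preferable.
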